##### Responsiveness to change

To explore the responsiveness of the PCSS, study participants will be categorized into three groups based on responses to a question about their global impression of symptom change from baseline to 3 months (Coon and Cook, 2018). Within each group (no change, worsened, and improved), the total PCSS score will be compared used a paired *t*-test. The standardized response mean will be computed as the mean change scored divided by the standard deviation of the change scores within each change category (worsening vs. no change vs. improvement). Values greater than 0.8 will be considered large and values between 0.5 and 0.8 will be considered moderate. Subsequently the change in total score will be investigated using analysis of covariance in which the T1 score is a covariate and change in symptom severity (worsening vs. no change vs. improvement) is a factor in modeling the T2 rating. Lastly, change scores will be modeled using a generalized linear regression model. cGVHD severity scores and change in PedsQL physical function scores will be incorporated into this model in confirmatory analysis. These various approaches to examining responsiveness to change will be triangulated to preliminarily propose clinically meaningful thresholds for change at the individual and group level (Trigg and Griffiths, 2021).

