#### Data collection procedures

After enrollment, the child participant and their caregiver-proxy will be provided with their own unique secure electronic link to independently complete the study measures [PCSS, PedsQL general (Varni et al., 2007c) and transplant modules (Lawitschka et al., 2014), and LSS; corresponding to their role (child or caregiver-proxy) and age band (5–7; 8–12, and 13–17 years); see Table 3 for a summary of the assessment schedule]. To examine test-re-test reliability, both the child and their caregiver-proxy will complete a second PCSS within 24–48 h of their initial completion of the measures (T2). To explore the responsiveness of the PCSS, study participants will complete the PCSS and PedsQL (general and transplant module) approximately 3 months (T3) after enrollment. They will also be asked to indicate whether their cGVHD symptoms have worsened, are unchanged, or have improved. Caregiver-proxy participants may assist their younger child (ages 5–7 and 8–12 as warranted) in completing this global assessment of change in cGVHD symptoms. Respondents ages 13–17, and their caregiver-proxies will also complete the LSS at all three timepoints. The measures are described in more detail in Supplementary Table 2.

**Table 3 tab3:** Summary of patient-reported outcomes by timing of assessment and age group (Phase 2).

Study assessments	Enrollment/Baseline	24–48 h after baseline	3 months after baseline

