##### Reliability

For test–retest reliability, we will examine the level of agreement between total PCSS score at T1 and T2 using the Intraclass Correlation Coefficient (ICC) in all respondents, within 3–5 days of their initial completion. We will evaluate at T2 if by child and caregiver-proxy report the child remains in stable health and with stable symptoms of cGVHD (Qin et al., 2019). The ICC will be computed based on a two-way, mixed effects analysis of variance model (Shrout and Fleiss, 1979; Liljequist et al., 2019). ICC ≥ 0.70 will be interpreted as demonstrating adequate test–retest reliability.

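### Responsiveness ANCOVA: the outcome visit must be reconciled to T3, after which the T1/T2 mean would be a modestly better baseline covariate than T1 alone (minor)

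*Protocol article*

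**What the plan says.** The responsiveness analysis sorts participants into worsened, unchanged and improved by their own "global impression of symptom change from baseline to 3 months". After paired t-tests and standardized response means within each group, the Protocol article (Responsiveness to change) specifies an "analysis of covariance in which the T1 score is a covariate", in which the three-level change category "is a factor in modeling the T2 rating".

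The section Data collection procedures places the responsiveness assessment at "approximately 3 months (T3) after enrollment". The same section says that "both the child and their caregiver-proxy will complete a second PCSS" 24–48 hours after the first, and labels this T2. The section Reliability gives T2 its purpose: "we will examine the level of agreement between total PCSS score at T1 and T2". There, however, the window is "within 3–5 days of their initial completion". That section accepts an ICC of 0.70 or more as adequate and checks at T2 whether the child's health and symptoms are stable.

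The ANCOVA is one of several approaches combined to suggest provisional thresholds for meaningful change.

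**The concern.** Two things in one sentence need attention.

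1. **Outcome.** The factor describes change over 3 months, but the modelled score is taken a few days after baseline. A model of T2 contains no 3-month change.
2. **Covariate.** With the outcome read as T3, the change groups are still not randomised and may differ at T1. Eligibility mixes children on systemic treatment with children off it for up to 12 months, and item scores have a floor, so a child with little bother at T1 has little room to improve. A difference at T1 is therefore plausible, though its size is unknown. ANCOVA removes such a difference only as far as the covariate is reliable. A single questionnaire total is less reliable than the mean of two taken days apart, and both are already collected.

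At stake is the ANCOVA's contribution to the proposed thresholds. Raw change scores do not suffer this attenuation. With a difference at T1, the approaches could disagree partly because of measurement error, and that could be mistaken for real uncertainty about the threshold.

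**Working it through.** **The plan's own figures.** The article states no power, SD, effect size or precision for this ANCOVA. Its only precision figure is for a Pearson correlation of 0.8 with n = 120. The Fisher interval, tanh(atanh(0.8) ± 2.576/√117), gives 0.697–0.871, which reproduces the stated 99% interval of 0.70–0.87. It has no bearing on the ANCOVA.

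**Inputs.** From the article: T1 as covariate, T2 within days, T3 at about 3 months, 120 dyads, ICC acceptance threshold 0.70. Assumed, because the article gives no values: reliability 0.70–0.90, true-score T1–T3 correlation 0.5–0.9, a true T1 gap between improved and unchanged of 0–0.5 SD, and a true group effect of −0.50 SD.

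**Step 1: the text as written (T2 as outcome).** With no true change between T1 and T2, the expected group contrast is (1 − reliability) × gap. At reliability 0.70 this is 0 with no gap, 0.3 × 0.3 = 0.09 with a gap of 0.3 SD, and 0.3 × 0.5 = 0.15 with a gap of 0.5 SD. Simulation (three groups of 40, 4,000 runs) gave −0.002, 0.097 and 0.152. The model returns nothing, or an artefact of the gap.

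**Step 2: outcome read as T3, bias.** The uncorrected amount is (1 − R) × slope × gap. R is the reliability ρ for T1 alone, and 2ρ/(1 + ρ) for the T1/T2 mean if the errors are independent. The estimates below take slope 0.7, gap 0.5 SD (improvers higher) and true effect −0.50, with simulated values in brackets.

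| ρ | Uncorrected, T1 alone | R of mean | Uncorrected, mean | Estimate, T1 alone | Estimate, mean |
|---|---|---|---|---|---|
| 0.70 | 30% | 0.824 | 17.6% | −0.395 (−0.397) | −0.438 (−0.439) |
| 0.80 | 20% | 0.889 | 11.1% | −0.430 (−0.428) | −0.461 (−0.460) |
| 0.90 | 10% | 0.947 | 5.3% | −0.465 (−0.468) | −0.482 (−0.485) |

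- With slope 1 instead of 0.7 and ρ = 0.70: −0.50 + 0.30 × 0.5 = −0.35 for T1 alone, and −0.50 + 0.176 × 0.5 = −0.41 for the mean.
- With no gap, both covariates give −0.50.
- If improvers start 0.5 SD lower, the sign reverses. At ρ = 0.70 and slope 0.7, T1 alone gives −0.50 − 0.105 = −0.605, away from zero.

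**Step 3: precision.** The residual variance is 1 − (ρr)² for T1 alone and 1 − ρ·R·r² for the mean, where r is the true-score T1–T3 correlation. At ρ = 0.70:

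- r = 0.5: 0.878 against 0.856; SE 1.2% lower, equal to about 123 children instead of 120.
- r = 0.7: 0.760 against 0.718; SE 2.8% lower, about 127.
- r = 0.9: 0.603 against 0.533; SE 6.0% lower, about 136.

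**Step 4: shared T1/T2 error.** Both scores use a 1-month recall and are taken days apart, so the recall windows nearly coincide and answers may be remembered. Suppose half of the error variance of 0.30 is shared. The error variance of the mean is then 0.15 + 0.15/2 = 0.225, and the uncorrected share is 0.225/(0.70 + 0.225) = 24%, not 18%. With slope 0.7 and gap 0.5 SD, the simulated estimate moves only from −0.39 (T1 alone) to −0.41 (mean).

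**The case against.** The strongest reply is that the sentence names T2 as the outcome, so T2 cannot also form part of the covariate, and the covariate point addresses a model that the article does not state. That stands for the literal text. For the same reason a reader should not infer that T2 is used for nothing but the ICC. The reply does not dispose of the point, because a retest outcome contradicts the 3-month change groups and the T3 responsiveness visit. Once the outcome is reconciled to T3, T2 is free to serve as a second baseline.

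A second reply is that a single baseline score is a standard covariate, that this analysis is exploratory and one of several, and that the paired t-tests and standardized response means do not use the covariate slope. All of this is true, and it limits the severity.

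A third reply is that 0.70 is an acceptance threshold and not an estimate of PCSS reliability, and that no T1 gap is reported. Also true: the percentages are conditional illustrations.

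A reader might also infer that a T1-only covariate lets a shift between first and repeat administration distort the result. In the ANCOVA a constant shift goes into the intercept and leaves the group contrast unchanged, so that argument gives no support here.

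**Conclusion.** The outcome visit is a contradiction within the article and must be reconciled. Conditional on T3 as the outcome, T1 alone is a serviceable covariate that data already collected can improve. The uncorrected share of any T1 gap would fall from 30/20/10% to about 18/11/5% at assumed reliability 0.70/0.80/0.90, before scaling by the true T1–T3 slope. The SE would fall by about 1–6% at reliability 0.70. Both gains shrink if T1 and T2 share error, and averaging reduces the bias without removing it.

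A reader might infer that the planned analysis does under-correct, that it biases effects toward zero, or that it wastes substantial precision. The documents support none of these. They give no T1 gap and no reliability estimate. The bias is toward zero only if improvers start higher, away from zero if they start lower, and absent without a gap. The precision gain is small. Severity: minor.

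**What to change.** 1. In Responsiveness to change, reconcile the ANCOVA outcome with the 3-month change groups and the T3 visit. Reconcile the two stated T2 windows (24–48 hours and 3–5 days) as well, since T2 would now also serve as a baseline measurement.
2. In the ANCOVA of the T3 score, use the mean of the T1 and T2 PCSS totals as the baseline covariate, with T1 alone if T2 is missing or the child is reported unstable at T2. Report the T1-only version alongside. Do this for both the child and the proxy form.

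The cost is one line of analysis wording and no new data. There are three drawbacks. The gain is small if T1 and T2 errors are correlated. The fallback mixes covariates of slightly different reliability. The covariate would also differ from the T1 baseline behind the paired t-tests and standardized response means. The T1-only version keeps the link to those analyses visible.

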Currently receiving systemic treatment for cGVHD (including phototherapies), or has tapered systemic therapy for cGVHD to discontinuation within the past 12 months					Children age 8–12 years: *N* = 40 patient-caregiver dyadsChildren age 13–17 years: *N* = 40 patient-caregiver dyads	T2 (24–48 h after enrollment)T3 (3 months after enrollment)	Congruence between symptom ratings provided by child participants and their caregiver-proxies will be explored.In subjects ages 13–17, we will also compare responses on the PCSS with those from the LSS, to determine the youngest age at which adolescents respondents can comprehend the LSS.				
English speaking											
Absence of severe cognitive or psychiatric disability that would impair the child’s capacity for participation or completion of study related procedures, in the judgment of the investigators								
Caregiver-proxies of participating children		Age older than 18 years						
		Caregiver-proxy of participating subject						
		Able to speak, read, and write English						

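### The responsiveness ANCOVA names the 24–48 h retest (T2) as its outcome, although its factor is change over 3 months and T3 is the visit collected for that purpose

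*Protocol article*

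**What the plan says.** The relevant statements are all in the protocol article.

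- **Responsiveness to change, grouping.** Participants are classed as worsened, unchanged or improved from "responses to a question about their global impression of symptom change from baseline to 3 months".
- **Responsiveness to change, model.** After the paired t-tests and standardized response means, change in total score is to be examined by an ANCOVA that adjusts for T1. Its factor and outcome are given as follows: "change in symptom severity (worsening vs. no change vs. improvement) is a factor in modeling the T2 rating".
- **Table 1, Phase 2 timepoints.** After T1 (baseline at enrollment) the table gives "T2 (24–48 h after enrollment)T3 (3 months after enrollment".
- **Data collection procedures.** For test–retest purposes, child and caregiver-proxy "will complete a second PCSS within 24–48 h of their initial completion of the measures (T2"). For responsiveness, "study participants will complete the PCSS and PedsQL (general and transplant module) approximately 3 months (T3) after enrollment".
- **Reliability.** The T1 and T2 total scores are compared by intraclass correlation, with a check at T2 that the child's health and cGVHD symptoms are stable.
- **Use of the results.** The responsiveness analyses are to be triangulated into preliminary thresholds for meaningful change at individual and group level.

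**The concern.** The factor and the outcome of the ANCOVA refer to different periods. The factor describes what happened between baseline and 3 months. The outcome is a score taken one to two days after baseline, at a point where the plan expects stability. A model of T2 given T1 compares short-term retest differences between children who will later report worsening, no change or improvement. That is not a comparison of how far their scores moved over the 3 months.

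Responsiveness and the minimally important difference are among the specific aims, and responsiveness is part of the primary objective of Phase 2. An analyst who followed the sentence literally would produce an uninterpretable result and carry it into the triangulation. An analyst who silently used T3 would depart from the published plan.

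**Working it through.** The protocol gives no effect size, power or precision figure for responsiveness, so there is no stated number to reproduce. The check is a comparison of timepoints, followed by a short look at what the literal model would estimate.

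**1. Timepoints side by side**

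| Element | Timing | Where stated |
|---|---|---|
| ANCOVA covariate | T1, baseline | Responsiveness to change |
| ANCOVA factor | change from baseline to 3 months | Responsiveness to change |
| ANCOVA outcome as written | T2 | Responsiveness to change |
| Meaning of T2 | 24–48 h | Table 1; Data collection procedures; the matching column of Table 3 |
| Purpose of T2 | test–retest, with stability check | Data collection procedures; Reliability |
| Visit collected for responsiveness | T3, about 3 months | Data collection procedures |

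Table 3 schedules the children's global self-assessment at baseline and 3 months, and not at 24–48 h. The Reliability section gives the retest window as 3–5 days, which conflicts with 24–48 h, but on either reading T2 is not the 3-month visit. The Responsiveness section never mentions T3.

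**2. What the literal model estimates**

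Write T1 = L + e1, T2 = L + e2 and T3 = L + C + e3. L is the underlying symptom level around baseline, C the change arising after T2, and the e terms independent errors. T2 does not contain C.

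- *If the change category depends on C only, and C is unrelated to L:* given T1, the category is independent of T2, so the expected group effect is 0 whatever the size of C.
- *If the category also reflects symptom level:* it carries information on L. T1 measures L with error, so adjustment for T1 does not remove it. With assumed SD(L) = 1 and error SD 0.4, the variance of L left after T1 is 0.16/(1 + 0.16) = 0.138, which is not zero. T2 can then differ between categories although no 3-month change enters it.

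In both cases the T2 model does not estimate C.

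**3. Illustration (assumptions not from the protocol)**

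The three-group F-test adjusted for T1 was simulated with 3,000 runs per setting: equal groups, 3-month shifts of ±0.3, ±0.5 or ±0.8 baseline SD, T1–T2 correlation 0.7 or 0.9, T1–T3 correlation 0.5 or 0.6, and no change before T2.

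| n | Shift (SD) | Rejection, T2 outcome | Rejection, T3 outcome |
|---|---|---|---|
| 120 | 0.3 | 0.044–0.055 | 0.789–0.850 |
| 120 | 0.5 | 0.047–0.049 | 0.996–0.999 |
| 120 | 0.8 | 0.048–0.053 | 1.000 |
| 90 | 0.3 | 0.046–0.054 | 0.630–0.718 |
| 90 | 0.5 | 0.049–0.054 | 0.981–0.993 |
| 90 | 0.8 | 0.039–0.058 | 1.000 |

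The mean estimated effect (first change group against no change) stayed within ±0.004 SD with T2. With T3 it recovered the assumed shift. The T2 column follows from the set-up, because groups were made unrelated to T1 and T2, so it illustrates step 2 and is not separate evidence. When the category was instead allowed to depend on current symptom level (n = 120, 40/40/20 split, error SD 0.4), rejection with T2 rose from 5% to 9%, 19% and 34% as that dependence increased.

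**The case against.** The strongest reply is that this is a slip of one label. The section opens with change from baseline to 3 months, the ANCOVA sentence is introduced as examining change in total score, and Data collection procedures ties T3 to responsiveness. Nothing suggests that anyone chose a 24–48 h outcome, and an alert analyst would probably use T3. That stands, and it limits the weight of the point. It does not remove it, because T2 is a defined label in this document and the sentence names the wrong visit.

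Three stronger readings are tempting, and the documents do not support them.

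- *Responsiveness would go unassessed.* A reader might infer this from the missing T3. The other three methods name no timepoint and follow the 3-month framing, so they can be read as T1 to T3.
- *The ANCOVA must return a null result however responsive the scale is.* This holds only if the change category is unrelated to underlying symptom level. If it tracks current symptoms, a non-null but spurious T2 effect is possible.
- *The proposed thresholds would be pulled toward zero.* The protocol states no weighting or averaging rule for the triangulation, so neither the size nor the direction of an effect on the thresholds can be derived. A near-zero ANCOVA estimate beside clear T1-to-T3 changes might equally expose the mistake.

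**Conclusion.** The point holds as an internal contradiction that makes one stated analysis wrong as written. The ANCOVA outcome is the short retest, while its factor is 3-month change. Taken literally, it would not measure 3-month change, and any group effect could not be interpreted as responsiveness.

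The scope is one of four responsiveness methods, and its result is one input to preliminary thresholds. The cause is most likely a label error, not a considered choice of analysis. The conclusion rests on the protocol's own timepoint definitions and on the plan's premise that T2 falls in a stable period. It does not rest on the simulated figures, whose inputs are assumptions.

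**What to change.** In the ANCOVA sentence under Responsiveness to change, replace T2 with T3 (3-month), so that the model is the T3 total PCSS score with the T1 score as covariate and the three-level change category as factor. Carry the same label into the statistical analysis plan. While editing, it would help, though it is not essential, to say that the paired t-tests, standardized response means and change-score regression use T3 minus T1.

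The cost is a text correction. Table 3 already schedules the PCSS at 3 months for all three child age groups and for caregiver-proxies, so no visit, data item or sample-size change is needed.

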## Ethical, equity, and regulatory considerations

Children of both genders and from all racial and ethnic groups are eligible for this study if they meet the eligibility criteria outlined in the study protocol. Children under the age of 5 are excluded because these children are unlikely to be able to understand and report on the concepts of symptom intensity and interference (Tomlinson et al., 2021), especially for symptoms such as muscle cramping, skin thickening, itching, shortness of breath, muscle/joint pain, and body image changes all of which are common in cGVHD. Non-English speaking participants are not included because at this initial stage of measure validation, it is important to first create a reliable and valid measure in English before it is put through the rigorous translation and linguistic validation process used to create versions of the measure in other languages. A finalized English language measure will not be available until after Phase 2 is completed; as such, this work provides the foundation for future studies to develop and test the PCSS for children and caregiver-proxies who speak languages other than English. Several design features of this multi-site study including representation from different geographic regions of United States and Canada and the use of remote interviewing techniques support our efforts to recruit a diverse population with respect to gender, race and ethnicity, socioeconomic status, and severity of cGVHD (Upadhyay and Lipkovich, 2020).

Parent/caregiver consent and child participant assent is obtained from each family. Where deemed appropriate by the consenting site investigator and the child’s parent(s) or guardian, the child will also be included in all discussions about the trial, and age-appropriate language will be used to describe the procedures and tests involved in this study, along with the risks, discomforts, and benefits of participation. The assent process will take place in conjunction with consent; therefore, in person and remote assent are permitted under the same circumstances as in person and remote consent. Children under 18 will provide assent for their participation in accordance with their institution’s local requirements and the assent process will be documented per local procedures. A waiver of the documentation of informed consent for caregivers of participants who will be completing questionnaires about their children and participating in cognitive interviews was granted by the IRB at the coordinating center.

Throughout the study, participants may be asked to discuss issues that are sensitive such as body image changes, and mood, and could experience distress as a result. To address this concern, study team members explain during the consent process that should this occur, an option to follow-up with a clinical team member will be provided.

Participant information is coded with an ID number. Project data will be stored in a password protected secure computing environment to ensure that only approved members of the research team will have access to these data.

